**Visits 2-12 (V2-V12)**

- **Visit 2 (V2):** Visit 2 (V2) will take approximately 45 minutes to complete. At V2, participants will be randomized to 8 weeks of abstinence with contingency management (CB-Abst: n=100) or non-contingent monitoring with no abstinence requirement (CB-Mon: n=100).

*Measures to be completed by participants:*

- Timeline Followback Interview (TLFB)
- Marijuana Craving Questionnaire – Short Form (MCQ-SF)
- Cannabis Withdrawal Scale (CWS)
- Drug Testing
- The Reasons of Living for Adolescents (RFL-A)
- Columbia Suicide Severity Rating Scale (C-SSRS)
- Patient Health Questionnaire-9 (PHQ-9)
- Pittsburgh Sleep Quality Index (PSQI)
- Family Psychiatric History (KSADS)
- Short UPPS-P Impulsive Behavior Scale (Short UPPS-P)
- Monetary Choice Questionnaire Delayed Reward Discounting (MCQ Delay Discounting)
- Adverse Events
- Concomitant Medications
- Social Network and Substance Use
- **Visit 3 – 4 (V3-V4):** Visits 3 – 4 will take approximately 15 – 45 minutes

*Measures to be completed by participants:*

- Timeline Followback Interview (TLFB)
- Marijuana Craving Questionnaire – Short Form (MCQ-SF)
- Cannabis Withdrawal Scale (CWS)
- Drug Testing
- Columbia Suicide Severity Rating Scale (C-SSRS)
- Patient Health Questionnaire-9 (PHQ-9)
- Adverse Events
- Concomitant Medications
- **Visit 5 – 11 (V5-V11):** Visit 5 – 11 will take approximately 45 minutes

*Measures to be completed by participants:*

- Timeline Followback Interview (TLFB)
- Marijuana Craving Questionnaire – Short Form (MCQ-SF)
- Cannabis Withdrawal Scale (CWS)
- Drug Testing
- The Reasons of Living for Adolescents (RFL-A)
- Columbia Suicide Severity Rating Scale (C-SSRS)
- Patient Health Questionnaire-9 (PHQ-9)
- Pittsburgh Sleep Quality Index (PSQI)
- Adverse Events
- Concomitant Medications
- **Visit 12 (V12):** Visit 12 will take approximately 45 minutes

*Measures to be completed by participants:*

- Timeline Followback Interview (TLFB)
- Marijuana Craving Questionnaire – Short Form (MCQ-SF)
- Cannabis Withdrawal Scale (CWS)
- Beck Anxiety Inventory (BAI)
- Drug Testing
- Connors ADHD Self-Report Index (ASRI)
- The Reasons of Living for Adolescents (RFL-A)
- Columbia Suicide Severity Rating Scale (C-SSRS)
- Patient Health Questionnaire-9 (PHQ-9)
- Pittsburgh Sleep Quality Index (PSQI)
- Adverse Events
- Concomitant Medications
- Social Network and Substance Use
- ***Exit Interview:** Phone call will take approximately 10 minutes.

*Measures to be completed by participants:*

- PHQ-9
- Exit interview questions

*this is an optional interview that will only occur for participants who express that they do not want to complete all study procedures

- At visit 12 all participants, regardless of group assignment, will be provided treatment and support resources.

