We will conduct a 10-week, multi-method, randomized study, and will recruit 200 school-based adolescents, ages 12-18 years, with daily or near daily cannabis use and current depressive symptoms. The study design is nearly identical to that used in another IRB approved protocol aimed at pilot data collection for the current protocol (#2021P002416), apart from minor modifications to the study population. Participants will complete 2 weeks of real-time EMA during baseline cannabis use (EMA Phase 1; Baseline Use as Usual) to quantify the temporal relationship between cannabis use and mood and SI, and the within- (e.g., concurrent other substance use, social context of use) and between-subject factors (e.g., average severity of cannabis use, depression and SI) that may moderate these linkages. To determine how depression and SI change across short- and longer-term cannabis withdrawal, participants will then be randomized to 8 weeks of monitoring (CB-Mon) or incentivized abstinence via contingency management (CB-Abst). A key aspect of the approach is that the 8-week period is long enough to observe true changes due to cannabis discontinuation, separate from effects of withdrawal and residual cannabinoid exposure that generally subside in 4 weeks. Both groups will complete 1 week of EMA in weeks 1 (EMA Phase 2; Randomized Withdrawal) and 8 (EMA Phase 3; Randomized Sustained Abstinence) of the randomized study period. During all 3 EMA phases, participants will receive 7-9 random, time-stamped prompts per day to ascertain mood and SI in the absence of acute cannabis use, proximal but prior to cannabis use, and during or shortly after cannabis use.

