**Assessment Techniques**

Participants will complete 12 study visits across ~10 weeks and three waves of EMA data collection. To minimize burden and maximize feasibility, study visits will be conducted in a private room at a participant’s school campus or local library, in lab settings, or virtually via video conferencing (via MGB-approved video conference platforms like Microsoft Teams or zoom). Visits will entail collection of urine samples for verification of self-reported use and abstinence verification (for CB-Abst post-randomization), as well as brief questionnaires and interviews on interim substance use, craving, and withdrawal. Questionnaires and surveys on mood symptoms and suicidal ideation (SI) will be conducted by study staff blinded to group assignment.

**Semi-Structured Interviews:** Substance use disorders and other psychiatric diagnoses will be queried at the baseline with past and current modules of the Mini International Neuropsychiatric Interview (MINI) Kid 7.0.2, which was designed as a brief structured diagnostic interview for the major psychiatric disorders across development in DSM-5 (Sheehan, Sheehan, & Shytle et al., 2010). We will evaluate for cannabis use disorder, major depressive disorder, as well as other Axis I diagnoses (including those specific to developmental populations). At the baseline visit, we will administer the Self-Injurious Thoughts and Behaviors Interview (Nock et al., 2007) to assess lifetime self-injurious thoughts and behaviors and confirm past month SI. We will also conduct the Columbia-Suicide Severity Rating Scale (Posner et al., 2011) at V1 to capture in-depth information about past month SI. At V2-12, SI and behavior since last visit will be determined with the Columbia-Suicide Severity Rating Scale *(alongside the primary corresponding EMA measure).* Interviews will be administered by trained study staff with established interrater reliability.

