**Termination of Participation**

Participants will be terminated from this study if they fail to comply with study procedures or if in the opinion of the principal investigator, can no longer safely participate.

1. **Risks and Discomforts**

**Potential risks in the study are considered minimal and include:** Psychosocial, Social and Legal Risks: There are no uncommon psychological, social, or legal risks associated with participation in this study. Periods of voluntary cannabis abstinence are not uncommon for adolescent users as they often take breaks for participation in sports, family vacations, etc. There is a slight risk that the questionnaires and interviews may contribute to temporary discomfort when participants are asked about distressing symptoms (e.g., suicidal thoughts). Notably, prior research has shown that answering questions about suicidal thoughts and actions does not increase psychological distress or increase one’s suicidal thoughts/behaviors (Reynolds et al., 2006). Nevertheless, a study staff member will monitor the EMA responses and in the event of significantly worsening depressive symptoms, suicidal thoughts, or behaviors (described in detail below), will alert a clinically trained staff member who will follow-up within 24 hours. A doctoral level clinician, including PI [name], will be on call should they be needed.

**Fitbit Risks:** Fitbits used for sleep and activity data pose minimal risk and do not alter the current level of risk for the main study. A small portion of people either find the device uncomfortable or have reactions to the device or band. Alternate material Fitbit bands will be ordered as needed.

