**Protocol non-adherence.** Analyses involving phase 1 and/or phase 2 of EMA data collection, will only consider CB-Abst participants who have biochemically-validated CB abstinence for two months because the goal is to study the effect of abstinence on change in mood and SI. If fewer than expected CB-Abst abstain from CB use for the full two months, we will form Helmert contrasts: those in CB-Mon (a), CB-Abst who do not abstain (b), and CB-Abst who abstain (c). The 1^st^ Helmert contrast will compare a to b+c and will be the intent to treat comparison. The 2^nd^ contrast will compare b to c, which corresponds to the post hoc sensitivity analysis of interest. Similar considerations will be made if participants in CB-Mon incidentally discontinue CB use during the study.

**Power analysis and justification of recruitment targets for the confirmatory cohort.** The R package ‘EMAtools’ (version 0.1.3; Kleiman, 2017) was used to determine the power for the proposed analyses. Preliminary analyses from the exploratory study found effect size estimates for significant effects ranged from 0.19 to 0.44, and that 77% of participants completed all phases of the study, completing on average 76% of all prompts. Estimates of the power were therefore computed to detect a weak effect (a Cohen’s d of .2) based on linear multi-level models using the nesting structure for the proposed EMA analyses and an intra-class correlation of .09. Table 1 shows the breakdown of estimates power based on the hypothesis being tested under two scenarios: 1) an ideal scenario with the full proposed number of participants and responses, and 2) a realistic scenario where 77% of participants complete 76% of entries.

Table 1: Power estimates by hypothesis and attrition scenario (ideal versus worse-case)

| Hypothesis | N (%) for sample size | N (%) of completed entries | Power |
| --- | --- | --- | --- |
| 1.1 - 1.2 | 200 (100%) | 112 (100%) | 99% |
|  | 154 (77%) | 85 (76%) | 93% |
| 2.1 - 2.2 | 200 (100%) | 224 (100%) | 99% |
|  | 154 (77%) | 170 (76%) | 94% |

1. **Monitoring and Quality Assurance**

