**Reporting Adverse Events (AEs)**

PI [name] will meet regularly with all study investigators to review the details of data acquisition and analysis as well as any minor problems. AEs will be assessed for each subject at every in-person visit. In the event of any minor or significant AE, the PI will be contacted immediately. The PI will be responsible for the generation of summary reports documenting this process and outcomes which will be included in the Continuing Review reports to the IRB. Serious AEs (events that are unexpected, and related or possibly related to the research and that indicate there are new or increased risks to subjects) will be reported by telephone or email to the Partners IRB according to current PHRC Adverse Event Reporting Policy. All AEs (if not serious) will be reported in writing to the Partners Human Research Committee via Insight. All information regarding experimental subjects will be kept in a locked drawer in PI [name]’s locked office. All data will be identified by a unique code number.

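### No C-SSRS or adverse event collection is scheduled at early exit, and the optional exit call does not, as worded, cover participants whom the PI terminates

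*Protocol*

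**What the plan says.** The list of visits 2 to 12 ends with an exit interview by telephone: "Phone call will take approximately 10 minutes". Its measures are the PHQ-9 and exit questions that are not reproduced. A footnote limits it: "this is an optional interview that will only occur for participants who express that they do not want to complete all study procedures". In the schedule table the exit column has two marks, PHQ-9 and Exit Interview. The C-SSRS and Adverse Events rows are blank there, but both are marked at every visit from V2 to V12.

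The text agrees with the table. Under Assessment Techniques: "At V2-12, SI and behavior since last visit will be determined with the Columbia-Suicide Severity Rating Scale". Under Reporting Adverse Events: "AEs will be assessed for each subject at every in-person visit".

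Termination of Participation gives two grounds, non-compliance and the PI's opinion on safety: "Participants will be terminated from this study if they fail to comply with study procedures or if in the opinion of the principal investigator". Outcomes Monitoring repeats the rule. Neither section attaches an assessment to it.

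On resources, the V12 entry says: "At visit 12 all participants, regardless of group assignment, will be provided treatment and support resources".

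Planned Safety Monitoring asks the DSMB to judge whether adverse events are more numerous in CB-Abst than in CB-Mon. It also has the PI review retention, reasons for drop-out and clinical outcomes.

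**The concern.** The arm comparison of adverse events is a stated safety purpose of the trial. It needs events to be ascertained equally in both arms up to the time each participant leaves. Here ascertainment stops at the last attended visit. What happens between that visit and exit has no scheduled route into the data, unless the exit questions happen to ask about it.

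Hypothesis 2.1 predicts that negative mood and suicidal ideation rise in CB-Abst during the first week of withdrawal. It is therefore plausible that exits, or the reasons for them, differ by arm. Participants stopped on safety grounds are the ones whose last interval a safety board would most want to see, and the exit call as worded does not reach them.

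**Working it through.** **1. Attrition figure.** Inputs: planned size, "will recruit 200 school-based adolescents, ages 12-18 years" (General Description of Study Design); completion in the exploratory study, "77% of participants completed all phases of the study" (power analysis paragraph).

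- Completers: 200 × 0.77 = 154, which reproduces the realistic scenario in the power table.
- Non-completers: 200 − 154 = 46, or 23 per arm if all leave after randomization and attrition is equal (both assumptions).

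**2. What is scheduled at exit for these 46.**

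- C-SSRS: 0 of 46.
- Adverse Events: 0 of 46.
- PHQ-9: the uptake of the optional call is not given. The range is 0 to 46; if half accept (an assumption), 46 × 0.5 = 23.

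**3. Length of the uncollected interval.** The schedule puts V1 to V12 at days 0, 14, 16, 19, 21, 28, 35, 42, 49, 56, 63 and 70. For someone who misses no visit before leaving, the time since the last visit is:

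- up to 14 days between V1 and V2 (before randomization);
- up to 2, 3 and 2 days between V2 and V5 (the withdrawal week);
- up to 7 days from V5 onwards.

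It is longer if visits were missed first.

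**4. Whether EMA covers it.** EMA runs on days 0–14, 14–21 and 63–70. The randomized period is 70 − 14 = 56 days, and the stretch without EMA is 63 − 21 = 42 days. For 42 of 56 days the weekly visit is the scheduled source of suicidality data, and it ends when the participant leaves.

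**5. Who the exit call reaches.**

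| Route out | Exit call as worded | C-SSRS or AE at exit |
|---|---|---|
| Participant says they do not want to complete procedures | Optional | Not scheduled |
| PI terminates for non-compliance | Not covered | Not scheduled |
| PI terminates for safety | Not covered | Not scheduled |
| Lost without saying so | Not covered | Not scheduled |

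**6. Effect on the arm comparison.** Let x and y be the numbers of early leavers in CB-Abst and CB-Mon, and p and q the mean numbers of events per leaver in the uncollected interval. The observed difference in event counts is the true difference minus (xp − yq). It is too small if xp > yq, too large if xp < yq, and unaffected if they are equal. The protocol gives none of the four quantities by arm, so the sign cannot be derived.

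**The case against.** The strongest reply is that much safety information survives and other safeguards exist.

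- **Data up to the last visit are kept.** Collection is densest in the withdrawal week, when worsening is predicted. This stands: the gap is the last interval only.
- **The exit call is not empty.** It has the PHQ-9, which the schedule groups under suicidal ideation and behavior (loosely, since the anxiety inventory sits there too), and exit questions that may touch on safety. This stands as an uncertainty, but it does not help those whom the call leaves out.
- **Other safeguards run.** Each participant has a safety plan made at baseline. High EMA intent ratings lead to a clinical check-in within 24 hours with parents notified. Parents, an emergency contact or a collateral contact can be approached. The PI reviews reasons for drop-out. These are real, but the check-in depends on EMA, and none of them schedules a C-SSRS or an adverse event form at exit.
- **The 46 is a ceiling.** Not completing all phases need not mean leaving before V12. Some may leave before randomization, since eligibility also requires about a 50% EMA response in Phase 1; they cannot affect the arm comparison. This stands.

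A reader might go further and infer that participants stopped for safety leave unassessed and without support. The documents do not say so. Their exclusion follows from the exit call's restriction and from silence in the termination sections, and a safety termination itself implies that the PI has made a judgment. A reader might also infer that early leavers are those getting worse, so that the arm difference is understated. The protocol gives no reasons for leaving by arm, and CB-Mon leavers lose the same interval.

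**Conclusion.** The point holds as a gap in the schedule. The protocol fixes an exit contact that is optional, omits two instruments collected at every other post-baseline visit, and does not by its wording cover PI terminations. This fits poorly with its own plan to compare adverse events by arm.

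The size is at most about 46 of 200 participants, assuming that the pilot's completion rate carries over and that every non-completer leaves early. Each loses the interval since the last attended visit, usually no more than 7 days after randomization unless visits were missed first. Bias in the arm comparison is possible if exits differ by arm; its direction and amount are unknown.

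Resources are a narrower matter. The V12 sentence addresses all participants but takes effect at a visit that early leavers do not reach. That is a wording conflict to reconcile. It does not show that early leavers receive nothing, given the baseline safety plan and the earlier substance use resources available to some CB-Mon participants.

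**What to change.** - In the exit interview entry and the schedule table, have the exit contact attempted for every participant who stops or is stopped, whatever the reason, with participants free to decline.
- Add to it, as data collection, the existing C-SSRS (since last visit) and Adverse Events forms, and mark both in the exit column.
- Reconcile Termination of Participation, Outcomes Monitoring, Reporting Adverse Events (which ties collection to in-person visits, whereas the exit contact is a phone call) and Planned Safety Monitoring with that schedule. Who is terminated, and how they are managed, is for the investigators; no rule is proposed here.
- Reconcile the V12 sentence on resources, which addresses all participants, with its restriction to that visit.

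The cost is protocol wording and a longer call using instruments and staff already in the study. If the two forms add 10 to 15 minutes (an assumption), the total for 46 participants is 46 × 10 = 460 to 46 × 15 = 690 minutes, or about 8 to 12 hours over the trial.

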**Assessment Techniques**

Participants will complete 12 study visits across ~10 weeks and three waves of EMA data collection. To minimize burden and maximize feasibility, study visits will be conducted in a private room at a participant’s school campus or local library, in lab settings, or virtually via video conferencing (via MGB-approved video conference platforms like Microsoft Teams or zoom). Visits will entail collection of urine samples for verification of self-reported use and abstinence verification (for CB-Abst post-randomization), as well as brief questionnaires and interviews on interim substance use, craving, and withdrawal. Questionnaires and surveys on mood symptoms and suicidal ideation (SI) will be conducted by study staff blinded to group assignment.

**Semi-Structured Interviews:** Substance use disorders and other psychiatric diagnoses will be queried at the baseline with past and current modules of the Mini International Neuropsychiatric Interview (MINI) Kid 7.0.2, which was designed as a brief structured diagnostic interview for the major psychiatric disorders across development in DSM-5 (Sheehan, Sheehan, & Shytle et al., 2010). We will evaluate for cannabis use disorder, major depressive disorder, as well as other Axis I diagnoses (including those specific to developmental populations). At the baseline visit, we will administer the Self-Injurious Thoughts and Behaviors Interview (Nock et al., 2007) to assess lifetime self-injurious thoughts and behaviors and confirm past month SI. We will also conduct the Columbia-Suicide Severity Rating Scale (Posner et al., 2011) at V1 to capture in-depth information about past month SI. At V2-12, SI and behavior since last visit will be determined with the Columbia-Suicide Severity Rating Scale *(alongside the primary corresponding EMA measure).* Interviews will be administered by trained study staff with established interrater reliability.

Participants will complete a timeline follow-back (TLFB) (Sobell et al., 1986) for frequency, quantity, and duration of nicotine, cannabis, alcohol, and any other recreational substance use. A 90-day recall period will be queried at the baseline visit, and a past week recall period will be queried at subsequent study visits; V2-12). Based on our decades-worth of experience conducting adolescent substance use research, we do not anticipate adolescents being unwilling to report on such activities despite substance use being illegal for underage persons. Our proposed protocol will use best practices for maximizing validity of substance use self-report, including guaranteeing confidentiality, utilizing interviews designed to aid recall via memory aids, training interviewers to standardize interviewing techniques and give instruction on developing rapport with the participant and probing incongruent answers, emphasizing the lack of consequences for accurately reporting substance use, and explaining the existence of external, objective validation of substance use via drug tests (Babor et al., 1987). Cannabis and other substance use is not highly stigmatized among adolescents (Roditis & Halpern-Felsher, 2015); therefore, the likelihood of underreporting is expected to be very low. Additionally, and as is our practice in our ongoing trials, participant self-reported substance use will be treated as strictly confidential and will not be disclosed to parents at any time (Gryczynski et al., 2019), except in cases of suspected serious harm to self or others (e.g., driving while intoxicated). This will be explicitly explained to parents and participants during the consent/assent process.

**Questionnaires:** Surveys will be administered via REDCap, a HIPAA compliant, web-based application hosted by Partners HealthCare designed to support data capture for research studies (http://rc.partners.org/edcredcap), at in-person visits (or virtually via MGB-approved video conference platforms like Microsoft Teams or zoom; V1-12). Construct areas queried include, for example: demographics; cannabis use of family cannabis withdrawal; current and past use of other substance of abuse (e.g., tobacco, alcohol); family rules about substance use; parental messages about substance use; quality of family communication; peer support; social integration; exposure to risky peer networks; self-esteem; coping; depressive, anxiety, and ADHD symptoms; delinquent behaviors; temperament; suicidal ideation; sleeping habits. To enhance reproducibility, measures were drawn from the PhenX Toolkit when available (Hamilton et al., 2011).

**Toxicology:** At all study visits, participants will provide a urine sample, which will be used to qualitatively screen for cannabis use as well as other substances of misuse and quantitatively screen for amount of THC metabolites in urine.

For visits conducted virtually (via MGB-approved video conference platforms like Microsoft Teams or zoom), participants will be given or mailed a qualitative testing and shipping kit. Participants will be guided through the steps of testing the urine sample collected at each visit and will be instructed on how to package the sample for shipment.

**Ecological Momentary Assessment (conducted between V1-V2, V2-V5 and V11-V12):** At baseline, participants will be guided through installing the EMA platform (MetricWire) on their iOS or Android smartphone. Support for app installation and EMA training will be provided throughout the study as needed by phone and via tutorial materials. Participants will be told that surveys will commence the next day and that they should use the app throughout the next 2 weeks in the same way as trained at baseline. During the EMA phases, participants will complete random prompts via MetricWire using a data sampling scheme similar to that used in prior studies (Shiffman et al., 2020). Participants will never be asked to complete >9 random EMA surveys/day. To enhance compliance, participants will be paid a $100 compliance bonus at the end of each EMA phase if ≥80% of random prompts are completed.

At the end of 2 weeks, the app will automatically discontinue EMA surveys. Two 1-week EMA phases will occur during the randomized period (weeks 1 and 8 post randomization; Figure 1). Staff will re-train participants on the EMA app prior to each of these EMA phases. Staff members will monitor EMA compliance and will reach out proactively to participants failing to meet criteria. After the third and final EMA phase, participants will be reminded that they will no longer need the EMA app, and that they can delete it (see figure 1 study schema for illustration of EMA administration periods).

All EMA surveys, regardless of phase of the study, will consist of short, multiple-choice items with logic-branched follow-up items. Within each of these surveys, participants will be queried on social settings and activities, cannabis and other substance use, mood, and suicidal ideation. See sections below detailing our plan for data monitoring to ensure safety in the event of SI exacerbation.

**Actigraphy Component (Fitbit): P**articipants will participate in a study component that collects sleep and activity data via a Fitbit Inspire 3. Participants will wear the watch after enrollment at Visit 1 through the Visit 12 (approximately 70 days after enrollment). To enhance compliance, participants will be paid a $25 compliance bonus at each of the three EMA phases data is available for 16/24 hours of 80% of days within that phase.

| **Passive Parental Consent** | **Parental/student consent/assent** |  | **Cannabis users in CM discontinue cannabis use** |  |  |  |  |  |  |  |  |  |  |  |  |
| --- | --- | --- | --- | --- | --- | --- | --- | --- | --- | --- | --- | --- | --- | --- | --- |
|  | **V0** |  | **BL (V1)** | **V2** | **V3** | **V4** | **V5** | **V6** | **V7** | **V8** | **V9** | **V10** | **V11** | **V12** | **Exit interview** |
| Days since Baseline |  |  | 0 | 14 | 16 | 19 | 21 | 28 | 35 | 42 | 49 | 56 | 63 | 70 |  |
| Fitbit Inspire 3 |  |  | x | x | x | x | x | x | x | x | x | x | x | x |  |
| Phone Screener | x |  |  |  |  |  |  |  |  |  |  |  |  |  |  |
| EMA Assessments  (x indicates when EMA assessment phases begin) |  |  | x | x |  |  |  |  |  |  |  |  | x |  |  |
| *Substance Use Questionnaires* |  |  |  |  |  |  |  |  |  |  |  |  |  |  |  |
| AUDIT |  |  | x |  |  |  |  |  |  |  |  |  |  |  |  |
| CUDIT |  |  | x |  |  |  |  |  |  |  |  |  |  |  |  |
| CWS |  |  | x | x | x | x | x | x | x | x | x | x | x | x |  |
| ECDI |  |  | x |  |  |  |  |  |  |  |  |  |  |  |  |
| MCQ-SF |  |  | x | x | x | x | x | x | x | x | x | x | x | x |  |
| MMM |  |  | x |  |  |  |  |  |  |  |  |  |  |  |  |
| TLFB |  |  | x | x | x | x | x | x | x | x | x | x | x | x |  |
| Substance Use History |  |  | x |  |  |  |  |  |  |  |  |  |  |  |  |
| *Suicidal Ideation and Behavior* |  |  |  |  |  |  |  |  |  |  |  |  |  |  |  |
| BAI |  |  | x |  |  |  |  |  |  |  |  |  |  | x |  |
| PHQ-9 |  |  | x | x | x | x | x | x | x | x | x | x | x | x | x |
| Columbia Suicide-Severity Rating Scale |  |  | x | x | x | x | x | x | x | x | x | x | x | x |  |
| RFL-A |  |  | x | x |  |  | x | x | x | x | x | x | x | x |  |
| SITBI-R |  |  | x |  |  |  |  |  |  |  |  |  |  |  |  |
| *Other Relevant Confounds and Covariates* |  |  |  |  |  |  |  |  |  |  |  |  |  |  |  |
| ASRI |  |  | x |  |  |  |  |  |  |  |  |  |  | x |  |
| Adverse Events |  |  |  | x | x | x | x | x | x | x | x | x | x | x |  |
| Concomitant Medications |  |  | x | x | x | x | x | x | x | x | x | x | x | x |  |
| Demographics |  |  | x |  |  |  |  |  |  |  |  |  |  |  |  |
| Family Psychiatric History (KSADS) |  |  |  | x |  |  |  |  |  |  |  |  |  |  |  |
| PSQI |  |  | x | x |  |  | x | x | x | x | x | x | x | x |  |
| MCQ Delay Discounting |  |  |  | x |  |  |  |  |  |  |  |  |  |  |  |
| Medical Psychiatric History |  |  | x |  |  |  |  |  |  |  |  |  |  |  |  |
| Child Behavior Checklist Youth Self Report (CBCL) |  |  | x |  |  |  |  |  |  |  |  |  |  |  |  |
| MINI (MDE and CUD) |  |  | x |  |  |  |  |  |  |  |  |  |  |  |  |
| UPPS-PS |  |  |  | x |  |  |  |  |  |  |  |  |  |  |  |
| Social Network and Substance Use |  |  |  | x |  |  |  |  |  |  |  |  |  | x |  |
| *Urinalysis Test* |  |  |  |  |  |  |  |  |  |  |  |  |  |  |  |
| Toxicology |  |  | x | x | x | x | x | x | x | x | x | x | x | x |  |
| *Exit Interview* |  |  |  |  |  |  |  |  |  |  |  |  |  |  | x |

